### Data recording and follow-up

All included patients will preoperatively fill in two questionnaires on quality of life (SF-36, short-form 36, and DASI, duke activity status index) and one questionnaire on gastro-intestinal complaints (GIC). Preoperatively, information on the following will be collected: age, sex, weight, height, American Society of Anesthesiologists (ASA) classification, smoking status, Revised Cardiac Risk Index (RCRI), chronic obstructive pulmonary disease (COPD)/asthma, diabetes mellitus, primary clinical diagnosis, medical/surgical history, number of previous laparotomies, type of previous laparotomies, number of previous laparoscopies, type of previous laparoscopies, and medication usage. A physical exam will be performed, which includes vital signs and laboratory collection (to include C-reactive protein (CRP), chemistry, hematology and coagulation) and a pregnancy test if the patient is premenopausal.

Classification of operative wounds based on the degree of microbial contamination, the number of serosal injuries and the number of inadvertent enterotomies will be noted in the source notes and CRF.

The type of abdominal closure (layered or mass fascia closure) and suture material used will be noted in the source notes and CRF.

Patients in both groups will receive the same postoperative treatment. Until patients are discharged, the following parameters will be collected: postoperative complications (superficial incisional surgical site infections, deep incisional surgical site infections, anastomotic leakage, intra-abdominal abscess, peritonitis, unexplained fever, fascia dehiscence, wound dehiscence, postoperative hemorrhage, postoperative ileus (POI), pulmonary embolism, pneumonia, urinary tract infection, sepsis, and death), reoperations, first post-operative day of oral food intake, parenteral feeding, number of days parenteral feeding required, tube feeding, number of days tube feeding required, first post-operative day of passing flatus, first post-operative day of passing stool, usage of medication including pain medication, daily VAS-scores, hospital stay, Intensive Care Unit stay and Recovery Unit stay.

Patients will return 8 to 16 weeks after index surgery to have their ostomy taken down. Clinical follow-up to obtain update(s) on adverse events (AE’s), adhesion-related events, changes in concomitant medications, the presence/absence of surgical site infection (SSI) and the type of SSI (if applicable) will be done during the admission for ileostomy/colostomy takedown. Weight and vital signs will be noted and the following laboratory investigations will be repeated: CRP, sodium (Na), potassium (K), urea, creatinine, hemoglobin, white blood cell count, platelet count, international normalized ratio (INR) and prothrombin time (PT).

Patients in both groups will undergo the same procedure for ostomy closure. To evaluate the adhesions at the loop ileostomy/colostomy site, the incidence, severity and extent of adhesions around the ostomy have to be evaluated during takedown. The time required for takedown of the ostomy is defined as the time from start of the takedown to the time the bowel is repositioned in the abdomen, and this time will be noted on the CRF. The severity of adhesions will be scored according to the Zühlke classification (see Table 2). To assess the extent of adhesions, the ostomy is divided in four quadrants (Figure 2). The extent of adhesions is scored as the number of quadrants containing adhesions (Table 3). After the ileostomy/colostomy takedown is completed, the surgeon will introduce a laparoscope at the ostomy site and evaluate the incidence, extent and severity of adhesions at the incision site and at other areas potentially injured (and covered) during the initial procedure. The severity will be scored according to the Zühlke classification (see Table 2). The extent of adhesions underneath the incision site will be scored through estimation of the area covered by adhesions as a percentage of the total area underneath the incision. The incidence and severity of adhesions at other areas potentially injured during the initial procedure will be scored according to the Zühlke classification (see Table 2).

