### Outcome measures

The primary outcome measure will be the incidence of adhesions to the primary incision site or the specimen retrieval incision in the case of hand-assisted laparoscopy.

Secondary outcome measures on effectiveness are the extent and severity of adhesions to the primary incision site or specimen retrieval incision, incidence, extent and severity of adhesions at the loop ileostomy or loop/split colostomy site and of adhesions at areas potentially injured during the initial procedure, duration of ileostomy or loop/split colostomy takedown from the start of the takedown to the time the bowel is repositioned in the abdomen, percentage (%) of abdominal wall with adhesions, number of C-Qur™ barrier films used, sizes of C-Qur™ barrier films used, areas treated with C-Qur™ Films (underneath incision, ostomy bowel loops, other areas injured during initial procedure and considered adhesiogenic), reason for not placing film in one or more of the areas considered to be adhesiogenic, incidence of chronic abdominopelvic pain, incidence of other gastrointestinal complaints, quality of life as assessed by Short Form-36 and DASI, and total direct health care costs (30 days-in-hospital healthcare costs during both hospital stays).

Secondary outcome measures on safety are incidence of postoperative complications. Complications are divided into surgical and medical complications. Surgical complications are superficial incisional surgical site infections, deep incisional surgical site infections, anastomotic leakage, intra-abdominal abscess, peritonitis, unexplained fever, fascia dehiscence, wound dehiscence, postoperative hemorrhage, and postoperative ileus (POI). Medical complications are pulmonary embolism, pneumonia, urinary tract infection, sepsis, and death.

Other secondary outcome measures are reoperations, number of re-laparotomies, number of inserted central venous lines, other re-operations, first postoperative day of oral food intake, parenteral feeding, number of days parenteral feeding required, tube feeding, number of days tube feeding required, first postoperative day of passing flatus, first postoperative day of passing stool, usage of pain medication, daily VAS (Visual Analog Scale) scores, hospital stay, Intensive Care Unit stay, Recovery Unit stay, readmissions within 30 days after discharge, and in-hospital mortality.

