### Unblinding protocol

A Data Safety Monitoring Board (DSMB) meeting for safety assessment will be scheduled once every 15 patients have been enrolled. The study will be deblinded when there is a higher mortality rate or incidence of surgical complications than can be expected from data found in the literature. The deblinding will be performed by the same researcher who performs the randomization procedure.

Patients will be informed on request about the performed procedure only after completing the quality-of-life questionnaires 1 year postoperatively.

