### Analysis and sample size

It is hypothesized that the use of the C-Qur™ Film underneath the primary incision reduces the incidence of adhesion at the incision by 30%. This hypothesis is based on the supporting documentation for Seprafilm™ (treatment) versus Control (no treatment) with an adhesion rate of 94% in the control group and 64% in the treatment group [18–22]. We estimate a total drop out of 25% in this study, comprising 10% regular drop out and 15% drop out because of anastomotic leakage. A 15% drop out because of anastomotic leakages is chosen because it is the upper limit of the incidence of this complication. Assuming that the C-Qur™ Film group performs similarly to Seprafilm™, a total of 84 patients, (32 + 10 per group (25% drop out)) would be needed in a randomized study, with 80% power and two-sided alpha = 0.05 in order to detect a 30% reduction in incidence of adhesions.

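### The listed complications have no common observation window, and late events and post-discharge deaths in patients without takedown have no stated collection point

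*Protocol article*

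**What the plan says.** Outcome measures makes the incidence of postoperative complications the safety outcome. It lists surgical items (among them anastomotic leakage, abscess, deep infection and dehiscence) and medical items (among them sepsis and death), with no time window. Data recording and follow-up repeats the list and supplies the window: "Until patients are discharged, the following parameters will be collected: postoperative complications".

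Three other items reach beyond the index stay:

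- Outcome measures includes "readmissions within 30 days after discharge, and in-hospital mortality".
- Data recording and follow-up says "Patients will return 8 to 16 weeks after index surgery to have their ostomy taken down". An update on adverse events, adhesion-related events and surgical site infection "will be done during the admission for ileostomy/colostomy takedown".
- Randomization and blinding has a blinded ward physician collect postoperative parameters again after takedown.

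The one-year contact consists of questionnaires on quality of life and gastrointestinal complaints.

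Statistics compares total complication incidence, each separate complication and mortality between arms, again without a period. Analysis and sample size allows for 10% regular drop-out and "15% drop out because of anastomotic leakage". Unblinding protocol ties deblinding to mortality, or to a higher "incidence of surgical complications than can be expected from data found in the literature".

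**The concern.** An incidence can be interpreted only with its observation period. Here the itemised record ends at a patient-dependent event, discharge, and hospital stay is itself one of the listed outcomes. A patient who stays longer is observed longer.

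The takedown update would close much of this gap if everyone attended. But attendance depends in part on the very event of interest, since the plan expects leakage to be the main cause of drop-out. A patient who dies at home before takedown cannot attend at all.

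The stated aim covers safety as well as efficacy, and the Background singles out leakage as the harm seen with the comparable barrier. It also says the film clears in roughly 60 days, so late events are of interest. If late events are lost, the safety comparison under-counts them and cannot easily be set beside published rates that use a fixed window.

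**Working it through.** **Inputs (Analysis and sample size).** The total is 84 = 2 × (32 + 10). Expected drop-out is 25% = 10% regular + 15% leakage. Adhesion rates are 94% and 64%, two-sided alpha is 0.05 and power is 80%.

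**The plan's own figure.** The article gives no figure for the safety window. Its sample size reproduces: Fisher's exact test has 80.9% power at 32 per group and 79.0% at 31. This point does not depend on it.

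**Patients who may lack the takedown update.**

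- All drop-outs: 0.25 × 84 = 21. The plan's own allowance is 2 × 10 = 20.
- Leakage drop-outs: 0.15 × 84 = 12.6.
- Regular drop-outs: 0.10 × 84 = 8.4.
- Share of drop-out due to leakage: 12.6 / 21 = 60%.

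**Stated sources of safety data, side by side.**

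| Source | Content | Period | Needs takedown? |
|---|---|---|---|
| Index-stay record | Itemised complications, including death | Surgery to discharge | No |
| Readmission outcome | Readmission, not its cause | 30 days after discharge | No |
| Takedown update | Adverse events, adhesion-related events, surgical site infection | Once, at 8 to 16 weeks (56 to 112 days) | Yes |
| Ward record after takedown | Postoperative parameters | Stay after takedown | Yes |
| One-year contact | Questionnaires only | One year | No |

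Every stated source that records complications after the index discharge needs takedown. The one earlier post-discharge item that does not, readmission, does not record the complication.

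**Tracing patients through the table.**

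1. Leak before discharge: recorded, whatever happens later.
2. Leak after discharge, takedown takes place: the adverse-event update can record it.
3. Leak after discharge that leads to drop-out: presumably known as the reason for drop-out, but no stated rule counts it in the complication incidence.
4. Abscess, dehiscence or sepsis after discharge, no takedown: at most a readmission count.
5. Death after discharge and outside hospital, before takedown: outside the until-discharge list and outside in-hospital mortality, so no stated collection point.

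**Illustration under an assumption not in the article.** Suppose 10% to 50% of leaks appear after discharge. With a 15% leak rate, which the plan calls an upper limit, the index-stay record alone would show 0.15 × 0.90 = 13.5% down to 0.15 × 0.50 = 7.5%. In patients, 0.10 × 12.6 = 1.3 to 0.50 × 12.6 = 6.3 leaks would fall outside it. This is before any catch-up through takedown or the recorded reason for drop-out, so it overstates the final loss.

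**The case against.** Several parts of the opposing case stand.

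- **Collection does not simply stop at discharge.** The readmission count, the takedown update and the record after takedown all follow it. For the majority expected to reach takedown, late events have a route into the data.
- **Leaks in leakage drop-outs are mostly not lost.** A leak before discharge is on the list, and a leak that causes drop-out would normally be known as its cause. The gap is mainly other late events, and deaths. That these patients have no takedown at all is also an inference, because the article says only that they drop out.
- **A reader might infer a bias between arms.** The article does not support this. It states that postoperative care is the same in both groups, blinds the patient and the ward doctor who completes the record, and gives no reason to expect different stays. Even if the captured share of leaks were assumed to differ by 20 to 40 points, the spurious difference would be 0.15 × 0.20 × 42 = 1.3 to 0.15 × 0.40 × 42 = 2.5 patients per arm.
- **A reader might infer that the safety board's trigger is blunted.** The article does not say which data the board receives, nor which window the literature rates use, so this cannot be shown.

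The remaining argument is that this is a condensed article, and that adverse-event reporting and follow-up of drop-outs may be set out in the full protocol. That answers a complaint about silence. It does not fully answer this point, because the article states a collection rule that ends at discharge and ties the later update to takedown.

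**Conclusion.** The point holds in a limited form. The complications that make up the safety outcome are recorded over each patient's hospital stay, and the stated catch-up is conditional on takedown. About 21 of 84 patients, 12.6 of them for leakage, may not reach it. For them, late complications other than a known leak, and deaths after discharge, have no stated collection point. The incidences to be compared therefore lack a common window.

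The count of 21 rests on the plan's own drop-out rates and assumes that drop-outs do not attend takedown, so it is an upper figure. How many events would be missed cannot be derived from the article, and neither a bias between arms nor a failure of the safety trigger is shown. This is a cheap improvement to a secondary outcome; the primary adhesion analysis is unaffected.

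**What to change.** In Outcome measures, Data recording and follow-up, and Statistics, define each listed complication and mortality over one fixed window from the index operation, for example 30 days. Apply it to every randomised patient whether or not takedown takes place, and add a second summary up to takedown. Fill both from the index-stay record, the readmission records (including the reason for readmission) and the adverse-event update already planned. For patients without takedown, add a chart check or a telephone call. Count a leak given as the reason for drop-out as an event when it falls in the window. Use the same window in the summaries for the safety board.

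The cost is one definition and a chart check or call for about 21 of 84 patients. No procedure is added and clinical management does not change. Trial status says inclusion has not begun, so the change can apply to every patient.

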**Table 2 Tab2:** **Adhesion classification system according to Zühlke**
[16]

Score	Observation
0	No adhesions
1	Adhesions that are filmy and easy to separate by blunt dissection
2	Adhesions where blunt dissection is possible but sharp dissection necessary, beginning vascularization
3	Lysis of adhesions possible by sharp dissection only, clear vascularization
4	Lysis of adhesions possible by sharp dissection only, organs strongly attached with severe adhesions, damage of organs hardly preventable

For patients randomized to the C-Qur™ Film arm, the C-Qur™ Film must be applied to the viscera underneath the primary or specimen retrieval incision in case of hand-assisted laparoscopy. Preferably, the C-Qur™ Film is also applied to other areas considered to be adhesiogenic, such as the peritoneal dissection planes and the ileum or colon at the ostomy site. The number of C-Qur™ Film sheets placed in the abdomen is limited to a maximum area of coverage of 774 cm^2^. In case sheets of the largest size (15 cm × 12.5 cm) are used, the maximum is four sheets (Table 1). The application of C-Qur™ Film directly to a fresh bowel anastomosis is not allowed.

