### Randomization and blinding

Intra-operatively, the treating surgeon judges whether the patient is eligible for definite inclusion. Prior to formation of the temporary loop ileostomy, loop or split colostomy, included patients will be randomized. Patients will be randomized in a 1:1 fashion to the C-Qur™ Film arm (treatment arm) or the control arm. The randomization will be stratified by operative technique (open or hand-assisted laparoscopy). The allocation sequence will be computer-generated through the web-based program Alea©. A researcher who does not participate in the data analysis will manage the randomization process. This way, the researcher who will perform the data analysis is blinded from treatment allocation. Concealment of treatment allocation and blinding of the surgeon performing the index procedure is not possible because the patient will either get the intervention or does not get an intervention at all. Randomization will be noted in the operation reports, allocation will not.

The patient and doctor at the surgical ward who will complete the case report form during the post-operative period is blinded from treatment allocation. To achieve blinding during the data collection of outcome parameters, the surgeon who will perform the ostomy takedown procedure, will not be the same surgeon as the one who performed the index procedure. Because of the absence of clinical notes regarding allocation, however, the initial surgeon is allowed to do the ostomy takedown in case of man-power or organizational problems.

During the postoperative period after the ostomy takedown, the physician at the ward, who will collect the data regarding the post-operative parameters, will be blinded from the treatment allocation of the patient. The patient will stay blinded for the received treatment.

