### Statistics

In general, for continuous variables, the mean, standard deviation, median, IQR, minimum and maximum values will be presented. Groups will be compared using the *t*-test or Mann-Whitney *U* test, as appropriate, based on the distribution of the data. For categorical variables, the frequencies and percentage within each category will be calculated. Groups will be compared using the chi-square or Fisher’s Exact test, as appropriate, based on the expected counts. All available data will be summarized. Demographics, preoperative, perioperative, and postoperative parameters will be reported and compared for both groups. Descriptive statistics will be presented to describe the trial results. Missing data will be evaluated by the investigators, and appropriate action will be undertaken*.* In case of skewed baseline data between groups, results will be corrected for this data.

Our primary analysis will focus on the effectiveness and safety of the C-Qur film between the treatment group and the control group. A chi-square or Fisher’s Exact test will be performed to assess a significant improvement in the incidence, on the Zühlke score of adhesions underneath the incision site, underneath the loop ileostomy or loop/split colostomy site, and for the extent of adhesions underneath the loop ileostomy or loop/split colostomy site as well. The extent of adhesions underneath the incision site and the time needed for takedown of the ileostomy or loop/split colostomy will be compared using a *t*-test. To assess the safety of the C-Qur film the total incidence of postoperative complications will be compared using a *t*-test or a Mann-Whitney *U* test. The mortality and the incidence for each separate complication will be compared using a chi-square or Fisher’s Exact test.

Subgroup analysis will be performed on laparoscopic versus open colorectal resection, and on ileostomy versus colostomy for the incidence, extent and severity of adhesions as described above. Since data collection of the outcome parameters is not blinded when the same surgeon who performed the index procedure also takes down the ostomy, subgroup analysis will be performed for patients with and without blinded data collection of outcome parameters.

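### Takedown time includes the ostomy-site adhesion evaluation and probably the bowel closure, which adds noise to a secondary effectiveness outcome

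*Protocol article*

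**What the plan says.** Outcome measures lists, among the secondary outcomes on effectiveness, "duration of ileostomy or loop/split colostomy takedown from the start of the takedown to the time the bowel is repositioned in the abdomen". Data recording and follow-up repeats the same start and stop: the time is "defined as the time from start of the takedown to the time the bowel is repositioned in the abdomen", and it goes on the CRF. Statistics says that "the time needed for takedown of the ileostomy or loop/split colostomy will be compared using a" t-test.

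Three other statements decide what falls inside that interval:

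- At the ostomy site, "the incidence, severity and extent of adhesions around the ostomy have to be evaluated during takedown". This means a Zühlke grade (Table 2) and a count of quadrants with adhesions (Table 3). Nothing says that the clock is paused.
- The incision and other areas are assessed afterwards: "After the ileostomy/colostomy takedown is completed, the surgeon will introduce a laparoscope at the ostomy site".
- On closure, "Patients in both groups will undergo the same procedure for ostomy closure". The article does not say whether the bowel is closed before or after it is repositioned.

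**The concern.** Takedown time serves as an effectiveness outcome because an ostomy with fewer adhesions should be quicker to free. The clock stops later than that, when the bowel is back in the abdomen. It therefore also counts a research task, the ostomy-site evaluation, and any closure done before repositioning. The film has no evident route to shorten the closure, which follows the same procedure in both arms.

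Two things are at stake. First, minutes unrelated to adhesions add variance, so a real saving in dissection time is harder to detect with about 32 evaluable patients per arm. Second, the stop point leaves room for interpretation. The trial has five centers and mixes loop ileostomies with loop and split colostomies. If some surgeons close before repositioning and others after, they would record different intervals under the same definition.

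**Working it through.** **The plan's own figure.** The article gives no mean, SD, expected difference or power for takedown time, so there is nothing of its own to reproduce for this outcome. The only sample-size figure is 32 evaluable per group, for incision adhesions at 94% against 64% (Analysis and sample size). It reproduces: exact power of Fisher's test at two-sided 5% is 0.790 with 31 per group and 0.809 with 32. I use 32 per arm below.

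**What is inside the clock.**

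| Activity | Inside the interval? | Basis |
|---|---|---|
| Freeing the ostomy bowel | Yes | Definition of takedown time |
| Ostomy-site grade and quadrant count | Yes | Required during takedown; no pause stated |
| Bowel closure | Probably | Inferred from the stop point; order not stated |
| Laparoscopic scoring of incision and other areas | No | Done once takedown is completed |

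**Dilution.** Let freeing time have SD s and a true difference D between arms. Let the added time be independent of it, have SD k and have the same mean in both arms. Then:

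- expected difference for the whole interval = D, unchanged;
- SD for the whole interval = √(s² + k²);
- noncentrality of the t-test = D / (SD × √(2/n)). With n = 32, √(2/32) = 0.25. There are 62 degrees of freedom, two-sided 5%.

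All of the following inputs are assumptions: D = 8 minutes, s = 10 or 12, k = 0 to 15. First line as an example: 8 / (10 × 0.25) = 3.2, which gives power 0.883.

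| Added SD k | SD (s = 10) | Power | SD (s = 12) | Power |
|---|---|---|---|---|
| 0 | 10.0 | 0.883 | 12.0 | 0.747 |
| 3 | 10.4 | 0.855 | 12.4 | 0.721 |
| 5 | 11.2 | 0.804 | 13.0 | 0.678 |
| 10 | 14.1 | 0.606 | 15.6 | 0.523 |
| 15 | 18.0 | 0.416 | 19.2 | 0.375 |

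The 8 minutes has no anchor in the article. Film at the ostomy is not even compulsory ("Preferably, the C-Qur™ Film is also applied to other areas considered to be adhesiogenic"), so the true difference could be smaller. What does not depend on D is the shrinkage of the standardized difference, by the factor s / √(s² + k²). For s = 10 it is 0.89 at k = 5, 0.71 at k = 10 and 0.55 at k = 15.

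**Possible bias.** Suppose scoring takes m extra minutes when adhesions are present, and the ostomy-site incidence differs by 30 percentage points. That figure is borrowed from the incision hypothesis, since none is given for the ostomy. The shift in the mean difference is 0.30 × m: 0.3 minutes for m = 1 and 1.5 minutes for m = 5, in favour of the film.

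**The case against.** The strongest reply is that the definition is consistent. Outcome measures and Data recording and follow-up use the same start and stop, and start-to-repositioned is a legitimate pragmatic total. That stands: this is a weakness in what the outcome captures, not a contradiction.

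Closure inside the clock is nowhere stated. That also stands, and it matters, because the larger power losses need closure to be included. The inference is still reasonable. The stop point is repositioning rather than completed mobilisation, and the laparoscope enters through the ostomy site only once takedown is over. Silence on the order is itself worth repairing.

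The ostomy-site evaluation may take little separate time. A Zühlke grade is defined by how adhesions yield to blunt or sharp dissection, so the surgeon largely learns it while dissecting, and the quadrant count is brief. This stands too. If scoring alone is added, an SD of 3 to 5 minutes costs only about 3 to 8 points of power.

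A reader might infer two stronger claims. One is that all of the trial's adhesion scoring, including that for the primary outcome, is timed. The article places the laparoscopic scoring after takedown, so it is not. The other is that the outcome is biased towards the film. Both arms have the same evaluation and closure, and no passage says that scoring is slower when adhesions are present. One route remains: "the initial surgeon is allowed to do the ostomy takedown in case of man-power or organizational problems", so an unblinded surgeon could sometimes be scoring while the clock runs. Statistics already plans a subgroup analysis by blinded data collection.

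**Conclusion.** The point holds as a loss of precision and clarity in one secondary outcome. The interval certainly includes the ostomy-site evaluation and probably the closure. Any such time that is independent of adhesions lowers the standardized difference; that direction follows from the definition.

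The size rests entirely on assumed values. Under those used here, power falls from 88% or 75% to 80% or 68% with an added SD of 5 minutes, and to 61% or 52% with an added SD of 10. The loss is small if only scoring is added and substantial if closure is inside and varies as much as the dissection. Bias is conceivable but cannot be quantified from the article. The assumed 0.3 to 1.5 minutes is small beside the assumed 8-minute effect.

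The primary outcome and the sample size are untouched. This is a worthwhile, inexpensive improvement rather than a flaw that threatens the trial.

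**What to change.** Trial status says that inclusion has not started, so the CRF can still be changed.

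1. Add one time point: ostomy bowel completely freed. Analyse start-to-freed as the adhesion-related takedown time.
2. Keep start-to-repositioned as the reported total, and state whether bowel closure falls inside it.
3. Leave ostomy-site scoring during takedown, as Data recording and follow-up requires. Log any minutes spent only on scoring, so that they can be subtracted. Postponing the scoring until the adhesions have been divided would conflict with that section and could weaken the ostomy-site severity and extent outcomes.

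The cost is one more clock reading per takedown and an occasional note of scoring minutes. Start-to-freed is less comparable with published total takedown times, which is why the total is kept. No treatment or surgical step changes.
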